### Outcome measures

The primary outcome is the additional variance explanation in the psychopathology of eating behaviour in the elite sports group by the indicators (∆R²) of our theoretical model of DE [16]. The criteria of the regression models will be measured (A) binary conducting clinical interviews (ED present or absent) and (B) continuous using an ED instrument (severity of ED symptomatology).

*A)* Clinical interviews serve as a reference test. Trained specialists will assess participants for EDs (anorexia nervosa, bulimia nervosa, binge-eating disorder, and others) using ICD-11 criteria [14] in a ~ 30-minute interview. Based on the indicator internalization of a sport-specific body ideal, including muscular body images that can potentially contribute to EDs in elite sports, the criteria for muscle dysmorphia proposed by Pope et al. [45] are also part of the interview. ICD-11 criteria will be evaluated using selected questions of the ED examination interview from Lichtenstein et al. [26], allowing a sports-specific exploration of the fear of weight gain or behaviours to prevent weight gain, weight and shape concerns, food-related loss of control, exercise behaviour, and compensatory behaviours. Additionally, performance enhancing substance use, obsessive healthy eating, and physiological consequences of low energy availability in elite sports like reduced sex drive or menstrual dysfunction are evaluated [26, 46, 47]. In addition to the identification of EDs associated with clinically relevant psychosocial and physical impairments, borderline cases will be documented as DE presentations [48]. In comparison to the ICD-10, the ICD-11 might facilitate diagnosis in men by removing the endocrine disorder criterion [14]. Neither the interviewers nor the participants are informed about the results of the index tests.

*B)* The Eating Attitudes Test 26 [EAT-26; [49] evaluates the frequency of DE behaviours on a 6-point-scale with a cut-off of 12.66 indicating clinical risk in athletes [50, 51]. The EAT-26 is administered at T0, T2 and T3 and is used as a measure of ED symptom severity in the hierarchical regression analyses.

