Self-reported DE will also be assessed by the Eating Disorder Examination Questionnaire [EDE-Q, [52] in both groups and by an additional third instrument only in the elite athlete group. The EDE-Q is a valid and reliable EDs instrument with 28 items and four subscales (restraint, eating concern, weight concern, shape concern). Participants indicate the frequency of eating behaviours over the past 28 days. In a Danish elite athlete cohort, the EDE-Q showed 90% sensitivity and 100% specificity with a cut-off of 2.3 [26]. The Brief Eating Disorder in Athletes-Questionnaire [BEDA-Q; [40] is validated for women athletes and consists of nine items indicating DE with a cut-off of 4 [40]. The first six items are adopted from the Eating Disorder Inventory 2 EDI-2 [53] and can be rated on a 6-point-scale. The three last items capture dieting regimes and frequency. The area under the curve (AUC) was 0.73 (98% CI, 0.52–0.93). Overlapping items of the instruments (e.g., Item 11 in the EAT-26 is the item 2 in the BEDA-Q and item 32 of the EDI-3) are only assessed once per survey. Both the EDE-Q and the BEDA-Q are used to assess the convergent validity of the EAT-26. They are not included as model criteria due to differences in assessment time points and item overlap with other instruments operationalising constructs in the theoretical model.

The regression models’ predictors consist of (C) sociodemographic-, health-, and sport-specific data, (D) the weight-sensitivity of the sports discipline, (E) the athletes’ perception of weight and shape pressure, (F) the internalisation of sport-specific body ideals (drive for thinness and muscularity striving behaviour), (G) training load, intentions and behaviours, and (H) the experience of fatigue and mood disturbances.

*C)* Sociodemographic data comprise sex, gender, age, nationality, occupation, and financial situation. Health data includes previous counselling or treatments and previous ED diagnoses. As the study targets elite athletes, the surveys include self-developed sport-specific items for elite athletes, such as sports discipline, current intention to modulate body weight, training phase and amount in their sports discipline. Controls are asked to report general training frequency and duration. Both groups indicate nutritional and movement data in general.

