*D)* The classification of weight-sensitivity into weight-sensitive (ballet) and less weight-sensitive (ball games) sports are adopted from Martinsen and Sundgot-Borgen [12]. The authors do not classify bodybuilding, but in this study it is considered a weight-sensitive sport, as the evaluation of physical appearance is regarded as the athletes’ performance [54, 55].

*E)* The Weight pressure in Sport Scale for men athletes [WPS-M; [56] and for women athletes [WPS-F; [57] are instruments that assess pressures from coaches and peers and include subscales specific to sex with 16 items for women and 14 items for men rated on a 6-point scale. In this study, items with the term “team members” is changed to “sport colleagues”, as most of the sports disciplines included in this study are individual sports.

*F)* Internalisation of body ideals is assessed by two validated instruments. The Muscle Dysmorphic Disorder Inventory (MDDI) measures the internalisation of a muscular body ideal [MDDI; [58] and includes 13 items across three subscales rated on a scale from 1 (never) to 5 (always). Based on the suggestion of Compte et al. [59], item five (“I think my chest is too small”) is adjusted to “I think my chest (muscle) is too small” to avoid the reference to breast volume [59]. The MDDI was used in an elite athlete cohort with men and women, showing good internal consistency (Cronbach’s α = 0.824), and categorizing individuals with scores ≥ 39 at risk for muscle dysmorphia [60, 61]. The internalisation of a thin body ideal is measured by the subscale of the Eating Disorder Inventory 3 Drive for Thinness [DT; [62, 63], which consists of 7 items rated on a scale from 0 (= never) to 5 (= always). Scores > 14 are considered as high DT [64]. EDI-3 items for weight history are used.

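### In the linear EAT-26 models, at least one response appears to be scored in both the criterion and the Drive for Thinness predictor, which raises that block's ΔR²

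*Protocol article*

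**What the plan says.** All quotations are from the protocol article, section Outcome measures.

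- **Primary outcome.** "The primary outcome is the additional variance explanation in the psychopathology of eating behaviour in the elite sports group by the indicators" (∆R²). It has a binary criterion (A, clinical interview) and a continuous one (B).
- **Criterion B.** "The EAT-26 is administered at T0, T2 and T3 and is used as a measure of ED symptom severity in the hierarchical regression analyses".
- **Predictor.** "The internalisation of a thin body ideal is measured by the subscale of the Eating Disorder Inventory 3 Drive for Thinness", "which consists of 7 items rated on a scale from 0 (= never) to 5 (= always"). Under Planned data analysis, the thin body ideal is listed as a block of its own.
- **Overlap.** "Item 11 in the EAT-26 is the item 2 in the BEDA-Q and item 32 of the EDI-3" is given as an example. Overlapping items "are only assessed once per survey".
- **Why EDE-Q and BEDA-Q are not criteria.** "They are not included as model criteria due to differences in assessment time points and item overlap with other instruments operationalising constructs". They serve convergent validity of the EAT-26 instead.
- **Schedule (Table 1).** EAT-26 is given at T0, T2 and T3, Drive for Thinness at T0 and T3, and BEDA-Q at all four time points. Drive for Thinness is the only EDI-3 scale in the table. The text adds only weight-history items from that inventory.

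Nothing in the article takes a shared item out of either score.

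**The concern.** If an answer is summed into the criterion and also into a predictor, the two scores covary through that answer whatever the relation between the constructs. The primary outcome is incremental variance explained, so the thin-ideal block gains some variance by construction. It is listed before the muscularity, training and fatigue blocks, so it can also take variance from them. The study exists to test whether this model holds, and one of its blocks would be tested with a favourable bias.

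The article's own reasoning points the same way. BEDA-Q is administered at every time point at which EAT-26 is, so timing alone does not separate the two. The remaining stated reason is item overlap, and the example given shows that EAT-26 has it too.

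**Working it through.** **1. Is the shared item in the predictor?** EDI-3 item 32 is not assigned to a subscale in the text. The only EDI-3 content used is Drive for Thinness (7 items) and weight-history items. The item is also an EAT-26 attitude item, so it very probably belongs to Drive for Thinness. This is an inference.

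**2. Is it the same response?** Yes, if criterion and predictor come from one survey (T0 or T3). The article does not name the time point of the primary regression. T0 is the natural reading: predictive validity is listed as a further objective, the EROS tool is given only at T0, and 2 × 146 = 292 of the 300 athletes are needed.

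**3. Is it handled elsewhere?** The multicollinearity checks, the composite indices and the separate-versus-composite sensitivity analyses all concern overlap among predictors, not between predictor and criterion.

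**4. The plan's own figure.** Test of R² increase with 6 tested and 9 total predictors, f² = 0.15, α = 0.05 and noncentrality 0.15·N. N = 146 gives power 0.9506, so the stated sample size reproduces. The planned effect is a partial R² of 0.15/1.15 = 0.130.

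**5. Size of the effect.** Assumptions, none of them in the document: equally weighted standardised items; correlation ρE among the other 25 EAT-26 items and ρD among the 7 Drive for Thinness items; latent correlation r; a shared item that reflects Drive for Thinness. With c = r√(ρE·ρD), and R² = Cov²/(Var EAT × Var DT):

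| Scoring | Cov | Var EAT | Var DT |
|---|---|---|---|
| Item in both | 175c + 1 + 6ρD | 26 + 600ρE + 50c | 7 + 42ρD |
| Removed from EAT-26 | 175c | 25 + 600ρE | 7 + 42ρD |
| Removed from Drive for Thinness | 150c + 6ρD | 26 + 600ρE + 50c | 6 + 30ρD |

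Example with ρE = 0.25, ρD = 0.6, r = 0.3, so c = 0.1162:

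- In both: 24.93²/(181.81 × 32.2) = 0.106
- Removed from EAT-26: 20.33²/(175 × 32.2) = 0.073
- Removed from Drive for Thinness: 21.03²/(181.81 × 24) = 0.101

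At r = 0.5 the three values are 0.248, 0.204 and 0.239.

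For ρE = 0.15–0.35 and ρD = 0.4–0.6, removal from EAT-26 lowers R² by 0.023–0.053 at r = 0.3–0.5, and by up to 0.055 at r = 0.7. Removal from Drive for Thinness lowers it by only 0.004–0.016 at r = 0.3–0.5. A simulation with skewed four-category EAT-26 items (loading 0.55) and Drive for Thinness items (loading 0.75) gives smaller drops: 0.023–0.033 and 0.004–0.009 respectively.

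**6. Error rate with no true association.** Simulation with n = 146, nine predictors and ρD = 0.5, nominal 5% test of the Drive for Thinness increment:

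| Scoring | Rejection rate |
|---|---|
| Item in both | about 9–13% |
| Removed from EAT-26 | about 4–6% |
| Removed from Drive for Thinness | about 8–11% |

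In this null case the inflation of R² itself is below 0.01.

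**The case against.** Five points can be made for the plan.

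- **Most of the R² change is content, not the duplicated answer.** This stands. If EAT-26 held an item of the same content answered separately, the covariance in the example would be 175c + 7ρD = 24.53 and R² would be 24.53²/(181.81 × 32.2) = 0.103, against 0.106 when the answer is shared. At r = 0.5 the gap is about 0.005. The rest arises because the criterion contains an item from the predictor's scale. That is still a fault in a ∆R² outcome, but the range above is an upper guide to the pure artefact.
- **The comparator is loose.** This stands. The figures are zero-order R² for one predictor, whereas 0.130 is a partial R² for six predictors after controls. They give scale, not a share.
- **EAT-26 overlaps less than BEDA-Q.** BEDA-Q takes six of its nine items from the EDI-2, while one of 26 EAT-26 items is named. Preferring EAT-26 is defensible as a matter of degree, but it does not justify leaving the known item in.
- **A lagged model avoids it.** With T0 predictors and a T2 or T3 criterion, wording is shared but the response is not. The article does not commit to such a model.
- **Scoring detail belongs in a fuller plan.** That is fair for routine scoring. Here, however, the article itself names the overlap and uses overlap as a ground for exclusion.

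A reader might also infer that the whole primary analysis is regressed on itself, or that several items are shared. The documents support neither. The interview criterion shares no questionnaire response, and only one item common to EAT-26 and EDI-3 is named. More are possible, since it is introduced as an example, but no figure for two or three items has a basis in the text.

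**Conclusion.** The point holds for the linear EAT-26 models when criterion and predictor come from the same survey. At least one answer appears to enter both, contrary to the article's own ground for excluding BEDA-Q. Under assumed loadings, the zero-order R² of Drive for Thinness is raised by roughly 0.02–0.03 at a latent correlation of 0.3–0.5, and by up to about 0.05 under other item correlations. With no true association, its 5% test runs at about 9–13%. The upward direction needs only positively correlated items; the size depends on the loadings. The conclusion also rests on item 32 belonging to Drive for Thinness. It is a bias in one block of one of the two criteria. It does not invalidate the primary objective or the sample size.

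**What to change.** - **List the overlap.** Before analysis, list every item that EAT-26 shares with any predictor scale, and state which time point feeds the primary linear regression.
- **Primary linear models.** Score the EAT-26 criterion without the shared items and keep Drive for Thinness intact. Removing them from Drive for Thinness alone can leave most of the inflation when the item reflects that construct.
- **Sensitivity analyses.** Report (a) both full scores and (b) full EAT-26 with the items removed from Drive for Thinness. Analysis (b) matters because the better side for removal depends on what the item measures. If it reflects the EAT-26 factor instead, removing it from Drive for Thinness lowered R² by 0.05–0.06 in simulation.
- **Convergent validity.** Compute the EAT-26/BEDA-Q correlation with the shared items removed from one scale, since the same answer inflates it.

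The cost is a scoring rule. No new data are needed, and 146 per sex is unchanged. The slightly shortened EAT-26 loses direct comparability with its published cut-off (12.66) in that model only. The full score remains available for the cut-off, ROC and prevalence analyses.

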### Sample size calculation

Sample size planning is based on the statistical verification of the primary objective. To estimate the required sample size, we conducted an a-priori power analysis using G*Power 3.1.9.7 [90]. We expect weight pressure, internalisation of a sport-specific body image, unhealthy training attitudes and behaviours, and physical and psychological fatigue symptoms to predict DE in athletes [16]. To assess the validity of the model, a hierarchical regression model will be computed for men and women respectively. Thus, the number of predictors tested will be six, and total predictors of the regression model include nine predictors with sociodemographic data. Effect sizes for men athletes were found to be smaller than for women athletes [91]. However, the strive for muscularity is not considered in most studies investigating DE in athletes, which has been described as a promising indicator to explain variance in ED symptomatology especially in men [92]. Consequently, effect size for men and women athletes are expected to be medium (Cohen’s *f*^2^ = 0.15) in the present study [3, 93]. The power for the sample size calculation was determined to 1-*ß* = 0.95. This results in a sample size of *n* = 146 for men and women athletes for the quantitative data assessment, respectively. Sample size per sports discipline (ballet, bodybuilding, and ball sports) will be balanced with approximately *n* = 100 each (total *n* = 300). For the comparison with the control group, *n* = 300 control participants are also sought.

The minimum sample size for the logistic regression was calculated using Wald’s-z test with fatigue as an exemplary predictor of least interest. The power curves showed the required sample sizes under variation of two parameters (see appendix Fig. 2). The minimum sample size for the logistic regression was balanced with the feasibility to perform clinical interviews with athletes who lack time due to strict training schedules while still reaching an acceptable power. Research findings on the prevalence of EDs in athletes range from 1.00 to 28.00% [3, 93], depending on sex, sport-discipline, weight-sensitivity of the sport, and self-report measures [94]. Rousselet et al. [93] considered that standard criteria are not reliable to diagnose EDs in athletes and revealed a proportion of athletes with an ED of 32.90%, independently of sex [93]. This prevalence is assumed to be realistic because modified ED criteria, such as those used in this study, could also capture the number of unreported cases. Hence, the prevalence of EDs in athletes as the base probability (*P*_0_) was estimated at 30.00%. It is assumed that variance explained by other covariates (*R*^2^ other) adds up to 20.00%. The effect size is estimated as medium odds ratio (OR) = 4.00 and the power is determined at 1-*ß* = 0.80 [95]. This results in a sample size of *n* = 43 for men and women athletes, respectively (*N* = 86). Thus, in bodybuilding, ballet, and ball games, approximately *n* ~ 30 interviews will be conducted, respectively.

Further, Receiver Operating Characteristic (ROC) curves and the AUC will be used to assess the diagnostic accuracy of individual and combined instruments to address the second aim. An AUC of 0.50 indicates no discriminative ability, values between 0.80 and 0.89 reflect good accuracy, and values between 0.90 and 1.00 indicate excellent accuracy. For each instrument or combinations of significant indicators from previous regression models, sensitivity (true positives / [true positives + false negatives]) and specificity (true negatives / [true negatives + false positives]), positive and negative likelihood will be calculated. To determine the optimal cut-off score for each instrument, Youden’s index [97] will be applied, identifying the point on the ROC curve that maximizes the sum of sensitivity and specificity (Youden’s J = Sensitivity + Specificity – 1). In addition, to minimize the risk of false negatives and thus the likelihood of overlooking athletes with clinically relevant eating pathology, alternative cut-off scores will also be evaluated by prioritizing a sensitivity of at least 80%, while maintaining an acceptable specificity threshold (e.g., ≥ 70%).

Significant predictors with the highest diagnostic accuracy will be included in logistic regression models as independent variables and ED diagnosis as dependent variable to calculate ORs. Based on this model, individual probabilities for the presence of an ED will be calculated for each participant in the athlete sample. The estimated prevalence is defined as the mean of these predicted probabilities. Mean differences of the probabilities (dependent variable) will be compared between the subgroups (independent variable) with ANOVAs for aim three. If the requirements for the analysis are not matched, we will conduct adequate alternative tests.

The *methodological examination* will be conducted by performing a measurement invariance using multi-group confirmatory factor analysis (CFA) to evaluate whether the factor structure of the ED instruments is equivalent between athletes and controls. ROC curves will be compared between athletes and controls, to assess if the identification of participants with or without an ED is better in controls than in athletes.

To identify risk or protective factors affecting DE over time as stated in *further aims*, among others linear-mixed models will be conducted. These models assume that data are missing at random (MAR). Attrition bias will be evaluated by comparing baseline characteristics between participants with complete and incomplete follow-up data. If systematic differences are observed, sensitivity analyses will be considered to assess the robustness of the findings.

Exploratory analysis may include interaction testing, pathway analysis (e.g., structural equation modelling), latent class models, or network analysis to examine complex relationships among predictors and ED symptoms. If systematic differences are observed between athletes participating in the clinical interviews and those participating in surveys only, inverse probability weighting may be applied as a sensitivity analysis to account for potential selection bias by weighting individuals according to their estimated probability of interview participation. If substantial overlap between related constructs is detected, sensitivity analyses using alternative operationalisations (e.g., separate versus composite predictors) will be conducted to evaluate model stability and robustness. Sensitivity– and subgroup analyses may additionally examine models combining clinically diagnosed EDs and subclinical DE presentations. Potential sex differences among athletes in the factor structure of ED instruments will be assessed through a measurement invariance analysis.

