### Objectives

The *primary objective* of the study is to evaluate the validity of the model for pathological eating in elite sport [16]. The indicators (weight-sensitivity, weight- and shape pressure, internalisation of a sports discipline-specific body ideal, unhealthy training intentions and behaviour, fatigue) specified in the model are expected to explain variance in ED symptomatology (measured by EAT-26) and/or increase the likelihood of an ED (clinical interviews) in elite athletes. The *second aim* is to investigate whether the diagnostic accuracy of ED identification in elite sports can be improved by combining standardized instruments (e.g., EAT-26) with sport-specific indicators (e.g., ART). The goal is to empirically derive cut-off scores that prioritize high sensitivity to minimize the risk of false negatives, while maintaining acceptable levels of specificity. The *third aim* is to estimate the prevalence of EDs in elite athletes by both the number of diagnosed cases in this cohort and ED instruments. The prevalence in weight-sensitive sports disciplines is hypothesised to be higher compared to less weight-sensitive sport-disciplines and compared to a control group. *Further study objectives* are the identification of protective factors (e.g., sport type, nutrition knowledge) for DE, the investigation of the predictive validity of the indicators, and the association of physiological markers (e.g., body fat percentage) with DE in elite sports. Methodologically, this study aims at investigating whether conventional instruments measure ED symptoms differently in elite athletes than in the control group.

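### Aim 2 asks whether detection improves, but cut-offs and combinations are re-derived in the same roughly 90 interviewed athletes, with no published athlete cut-off as a fixed reference

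*Protocol article*

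**What the plan says.** Objectives states aim 2 as a comparative question: "whether the diagnostic accuracy of ED identification in elite sports can be improved" when standardized instruments, with the EAT-26 as the example, are combined with sport-specific indicators such as the ART.

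Planned data analysis gives the method:

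- ROC curves and AUC are planned for single and for combined instruments.
- The main cut-off for each instrument comes from Youden's index, "identifying the point on the ROC curve that maximizes the sum of sensitivity and specificity".
- Combinations use indicators that were significant in the preceding regressions.
- In addition, further cut-offs are to be evaluated by "prioritizing a sensitivity of at least 80%, while maintaining an acceptable specificity threshold", for which 70% or more is given as an example.

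Outcome measures lists cut-offs that already exist. The EAT-26 is described "with a cut-off of 12.66 indicating clinical risk in athletes". For the EDE-Q: "In a Danish elite athlete cohort, the EDE-Q showed 90% sensitivity and 100% specificity with a cut-off of 2.3". The BEDA-Q has a cut-off of 4 and an AUC of 0.73. The EDE-Q and BEDA-Q are given the role of checking the convergent validity of the EAT-26. None of the three cut-offs appears in the aim 2 analysis.

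**The concern.** To show improvement one needs something to improve on. Here the new rules are tuned to the data on which they are judged. Each Youden cut-off is the best point in the interviewed sample. The indicators in a combination are selected by regressions whose data include those same athletes. A cut-off fixed before the study has no such advantage, and three of them are listed in the protocol, but the analysis does not call on them.

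Two things are at stake. The reported sensitivity and specificity of new cut-offs will be optimistic, and the comparison of new with existing practice will lean towards the new rule. Also, the article's premise that conventional criteria may not suit athletes would go unexamined at the cut-offs that the protocol itself cites.

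**Working it through.** **Inputs.** The interview sample is 90 (Abstract), about 30 in each of three sport groups; the calculated minimum is 43 per sex, so 86. Assumed prevalence is 30% (Sample size calculation). This gives 90 × 0.30 = 27 cases and 63 non-cases.

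**The plan's own figure.** The 43 per sex comes from a Wald z test for a logistic coefficient (base probability 0.30, OR 4, R² for other covariates 0.20, power 0.80). A recalculation with a normal predictor and one-sided 0.05 gives 42; a two-sided test without variance correction gives 53. Neither sidedness nor predictor distribution is stated in the text. Nothing below depends on this. It does show that the interview sample was sized for a regression coefficient, not for estimating or comparing accuracy.

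**Re-derived against fixed cut-off.** J = sensitivity + specificity − 1. The Youden cut-off maximises J over all cut-offs in the sample, and a fixed cut-off is one of the candidates. So apparent J(re-derived) ≥ apparent J(fixed) in every sample, whatever the truth.

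The size was simulated with 4,000 samples of 27 cases and 63 non-cases. Scores are equal-variance normal, and the fixed cut-off sits at the true optimum. The true optimal J is 2Φ(d/2) − 1, with d = √2·Φ⁻¹(AUC).

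| True AUC | True optimal J | Mean apparent J, re-derived | Excess |
|---|---|---|---|
| 0.70 | 0.289 | 0.376 | 0.09 |
| 0.80 | 0.448 | 0.523 | 0.08 |
| 0.90 | 0.635 | 0.697 | 0.06 |

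The true J of the re-derived cut-off is about 0.02 below the optimum (at AUC 0.80, 0.426 against 0.448). The re-derived cut-off looked at least as good as the fixed one in 100% of samples.

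**Combinations.** With the same 27 and 63, a base instrument at AUC 0.80 and a fitted logistic model, adding three pure-noise predictors raised the apparent AUC in about 90% of simulated samples; adding five did so in about 98%.

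**The 80%/70% targets beside the cited EDE-Q figures.**

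| | Target 80%/70% | Cited EDE-Q 90%/100% |
|---|---|---|
| J | 0.80 + 0.70 − 1 = 0.50 | 0.90 + 1.00 − 1 = 0.90 |
| Missed cases of 27 | 27 × 0.20 = 5.4 | 27 × 0.10 = 2.7 |
| False positives of 63 | 63 × 0.30 = 18.9 | 0 |

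If prevalence were 10% (assumption: 9 cases, 81 non-cases), the counts would be 1.8 missed and 24.3 false positives, against 0.9 and 0. The right-hand column carries another cohort's point estimates over to this sample, so it is a yardstick and not a forecast.

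**Precision.** Observed 22/27 gives an exact 95% CI for sensitivity of 62% to 94%. Observed 44/63 gives 57% to 81% for specificity.

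**The case against.** A reader might infer that the plan accepts any rule reaching 80%/70% and could therefore declare improvement for a rule worse than the EDE-Q. The text does not support that. Youden's index sets the main cut-off. The 80% and 70% figures guide additional cut-offs to be evaluated, the 70% is only an example, and nowhere is reaching them called success.

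The 90%/100% is also a weak basis for calling an 80%/70% rule worse in this study. It comes from one Danish cohort, with no interval shown, and nothing in the protocol assumes that it carries over to its own interview, which uses ICD-11 criteria and also covers muscle dysmorphia. The BEDA-Q, described alongside it, has an AUC of only 0.73. Under an equal-variance binormal assumption that implies a maximum J of about 0.34, below the 0.50 of the targets. No sensitivity or specificity is given for the EAT-26 at 12.66.

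Aim 2 does have an internal comparator: single and combined instruments are both assessed by AUC, and the AUC of a single named instrument needs no cut-off. This stands, but it does not settle the matter. The AUC of a fitted combination is optimistic in its own sample, as the noise-predictor check shows, and an AUC does not describe performance at a cut-off in use.

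Finally, a named paired test, intervals and internal validation may well be in a fuller protocol or SAP, so their absence here is not the point. The point is what the article does fix: cut-offs re-derived and indicators selected on the study's own data, for an aim about improvement. The simulation is also favourable to the fixed cut-off in placing it at the true optimum. A poorly placed published cut-off could be truly beaten, and a paired comparison would show that.

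**Conclusion.** The concern holds in a limited form. As written, the plan yields optimistic operating points and a comparison tilted towards the new rule, while leaving unused the one kind of operating point that needs no selection in this sample. The optimism in J is about 0.06 to 0.09, with a true loss of about 0.02. This assumes 27 cases and 63 non-cases, binormal scores, true AUC between 0.70 and 0.90, and a fixed cut-off at the optimum. That the re-derived cut-off cannot look worse in J needs none of these assumptions.

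The 80%/70% targets are not an acceptance rule. Because they lie below the EDE-Q performance that the protocol cites, reaching them would not in itself show improvement, and the text should say so. The change is worth making; it does not call the design or the data collection into question.

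**What to change.** In Planned data analysis:

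1. Also report sensitivity and specificity with exact 95% CIs at the published cut-offs (EAT-26 12.66, EDE-Q 2.3, BEDA-Q 4) in the same interviewed athletes.
2. Name one comparator in advance. The EAT-26 at 12.66 is a natural choice, since aim 2 names that instrument. Taking whichever published cut-off does best in the data would bring selection back in.
3. Base any claim of improvement on the paired differences in sensitivity and in specificity, with CIs, between the new cut-off or combination and that comparator. Correct the new rule for optimism first, for example by a bootstrap that repeats both the selection of indicators and the choice of cut-off.
4. State that 80%/70% is a minimum for screening use and not evidence of improvement.

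The cost is some wording and a few extra analyses on data already planned. With about 27 cases the paired intervals will be wide and improvement will be harder to claim. A note on timing is needed: Table 1 places the EDE-Q at T1 with the interview, while the EAT-26 is given at T0 and not at T1, so a comparison between the two instruments is not fully like for like.
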